## Methods

### Overview

This paper reports the research protocol for the SUSTAIN trial, including how we will partner with primary care, government, and pediatric hospitals to evaluate the effectiveness and cost-effectiveness of SUSTAIN in a cohort of general practices across NSW, using a stepped-wedge cluster RCT. The trial will be conducted according to the SPIRIT (Standard Protocol Items: Recommendations for Interventional Trials) checklist. We will apply the Medical Research Council framework used for developing and evaluating complex interventions [23].

### Trial Design

SUSTAIN is a stepped wedge cluster RCT of a virtual GP-pediatrician integrated model of care compared with standard GP care. This trial design has the rigor of a cluster RCT but allows all participating general practices to be exposed to the SUSTAIN care model, providing control, intervention, and postintervention data. This trial design was selected to ensure all practices receive the intervention [21] (Figure 1).

**Figure 1. F1:**

Stepped wedge randomized control trial design.

Each general practice provides control period data (referral and medical record data) during the control period (standard GP care, no SUSTAIN model operating). Each month thereafter, 3 practices switch concurrently from control to intervention where a pediatrician supports GPs through telehealth coconsultations, virtual case-based discussions, and being available by phone and email contact in working hours. During the first month of the intervention for each practice, a 1-month transition period is allowed to embed the SUSTAIN model of care into the practice, where data do not contribute to the analysis. This embedding period assists with implementation of the model of care into the practice and allows time to address any procedural issues. After the embedding period, each practice is exposed to an 11-month intervention period. Sustainability data are collected following cessation of the intervention until the intervention is completed for the final practice.

### Setting and Participants

SUSTAIN is a multisite trial conducted across GP practices in different local health districts within NSW. GP practices in both metropolitan and nonmetropolitan (regional, rural, and remote) areas of NSW, including areas with higher-than-average proportions of priority populations, will be eligible to participate.

Trial participants will include general practices with consenting GPs across NSW. Families of children <18 years attending the general practice may be asked to complete anonymous surveys regarding their experience of pediatric care in GP services.

Eligible general practices include those responding to an expression of interest and meeting the inclusion criteria (Textbox 1).

Textbox 1.Trial population exclusion and inclusion criteria.
**Inclusion criteria**
General practices:Be located within metropolitan and nonmetropolitan local health districts in New South Wales.Have best practice or medical director 3 as their electronic medical record.Be accredited or working toward accreditation against Royal College of General Practice standards.Agree to install GRHANITE software (for extracting general practitioner [GP] medical record data).GPs:See patients younger than 18 years.Provide a minimum of 2 weeks of referral data during the control period.Sign participant information consent forms.Families:Caregivers of children younger than 18 years who have received care at the general practice regardless of GP seen, in the prior 3 months for both the control and the intervention period.Caregivers with sufficient English to complete the survey.

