### Recruitment

#### General Practices and GPs

An expression of interest will be distributed to practice managers, GPs, and practice nurses through the primary health networks (PHNs) [24], Central and Eastern Sydney, South Western Sydney, South Eastern NSW, and directly to other general practices in rural, regional, and remote areas in NSW. Interested general practices will be required to sign a memorandum of understanding with the research team adhering to the requirements of their participation, and sign a license agreement to install the clinical data extraction software tool GRHANITE [25]. GRHANITE is discussed in the Data Management Plan section. Each GP will be required to sign a participant information consent form (Section S1 in Multimedia Appendix 1) to participate in the trial. Any GP wanting to participate during the intervention phase must provide at least 2 weeks of control referral data. Each participating practice will receive a one-off AU $1000 (approximately US $655) payment to support the implementation of the trial into their practice. An ethics-approved poster will be available for practices to promote the GP-pediatrician coconsultation service and inform patients about the study.

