### Randomization and Blinding

Participating practices will be randomized for intervention using a predetermined web-based randomization sequence generated by an independent trial statistician. Participating general practices will be randomly ordered in terms of when they switch from standard GP care to the SUSTAIN model of care by the independent statistician. To avoid recruitment bias in clusters, randomization will occur once all general practices have been recruited and enrolled; that is, after all inclusion and exclusion criteria are addressed, and all general practices sign the relevant trial agreements. Following randomization, practices will be unblinded to their allocation status/model of care start date. It is necessary for each general practice to know their randomization position to prepare for intervention, so allocation is not concealed. It is not anticipated that GPs knowing their randomization status will impact/change their standard practice due to their demanding workload. The research team is also unblinded to each practice’s allocation status to allow them to effectively engage with each practice to prepare their implementation schedule.

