### Data Collection

#### GP EMR Data Collection

To measure the primary outcome (ie, referrals to hospitals), pediatric referral data will be routinely collected from the GP EMRs via GRHANITE. This software will be remotely embedded into all participating GP medical software computers (compatible with BP or MD EMR software). For research purposes, GP data will be collected on all patients younger than 18 years. These data will be deidentified at the patient level, although the identity of the GP will be supplied to the research team. Collection of GP EMR referral data will commence for all practices following randomization and will continue for the duration of the trial.

The ability to record referral information, manage deidentification and consent processes, is a principal rationale for the use of the GRHANITE technologies and was demonstrated to be acceptable to GPs in the SC4C study [19].

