#### GP and Family Data Collection

GP and family survey data collection will occur preintervention (baseline) and in the last month of the SUSTAIN model of care (intervention) for each practice.

A web-based GP Survey (Section S3 in Multimedia Appendix 4) will be used to measure GP experience and confidence in pediatric care, completed by all participating GPs via REDCap. Based on the SC4C trial, the survey collects information including GP demographics, factors that impact their decision to refer a pediatric patient, and knowledge and confidence in pediatric care and services. GP name and general practice will be recorded for survey completion tracking, but will not be attached to the survey responses.

A web-based family survey (Section S4 in Multimedia Appendix 2) will be used to measure caregivers’ perceptions and experience of pediatric care provided at their general practice. To provide data on a “whole of practice” level, caregivers of a patient <18 years, regardless of whether they attended a consultation with a participating GP, will be eligible to complete the Family Survey via REDCap. The survey collects information on the child/family regarding a GP visit up to 3 months prior. These surveys are voluntary, and responses are anonymous.

No power calculation has been performed, as we will recruit as many families as possible during this timeframe and use all available data.

SUSTAIN GP and family surveys have been adapted from the SC4C study and comprise items generated by the SC4C investigators and drawn from previously published literature [19,30,31]. Data collection timepoints for participant enrollment and interventions can be found in Table 2.

**Table 2. T2:** Outline of participant enrollment, intervention, and data collection timepoints.

	Enrollment (–t_1_)	Allocation (t_0_)	Study period			Close out (t_x_)
			Control period (t_1_)	1-month Embedding period (t_2_)	11-month Intervention period (t_3_)	
Enrollment						
General practice eligibility screen	✓					
Informed GP^a^ consent	✓					
General practice intervention allocation		✓				
Intervention						
Virtual GP-pediatrician coconsultation				✓^b^	✓	
Virtual case discussions				✓^b^	✓	
Pediatrician phone/email support				✓^b^	✓	
GP access to SCHP^c^				✓^b^	✓	
Primary outcome						
GP referral outcomes						
GRHANITE extracted from routinely collected GP EMR^d^ data			✓	✓^b^	✓	
Secondary outcomes						
GPs						
Quality of care						

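### The claim that all inclusion criteria are settled before randomisation holds for practices but not for GPs, whose two-week data criterion can only be met afterwards, with start dates known

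*Protocol article*

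**What the plan says.** The statements sit in five places in the protocol article.

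- **Randomization and Blinding.** As a guard against biased recruitment, this section states that "randomization will occur once all general practices have been recruited and enrolled; that is, after all inclusion and exclusion criteria are addressed". It goes on to say: "Following randomization, practices will be unblinded to their allocation status/model of care start date". It also explains that practices need to know their position in order to prepare, "so allocation is not concealed".
- **Textbox 1, GP inclusion criteria.** "Provide a minimum of 2 weeks of referral data during the control period".
- **GP EMR Data Collection.** "Collection of GP EMR referral data will commence for all practices following randomization and will continue for the duration of the trial".
- **Recruitment, General Practices and GPs.** "Any GP wanting to participate during the intervention phase must provide at least 2 weeks of control referral data". No consent deadline is attached.
- **Table 2.** The row "Informed GP^a^ consent" is ticked under Enrollment, the column before Allocation.

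The Statistical Analysis section bases the intention-to-treat analysis on data from consenting GPs in randomised practices. It does not say whether consent must precede randomisation, or how a consenting GP who falls short of two weeks of control data is handled.

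**The concern.** In a stepped wedge trial with open allocation, enrolling participants before randomisation protects against selective entry. If GPs can qualify, fail to qualify or join once the start date is known, the mix of GPs in control months may differ from that in intervention months for reasons linked to the allocation. A GP who joins just before the switch would supply about two weeks of control data and up to 11 months of intervention data. A GP who consents but does not complete the two weeks might drop out of the comparison. Both steps would happen after randomisation, and the time for them differs by sequence. The article claims a protection that, at GP level, its own rules do not deliver.

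**Working it through.** **1. Order of events.** Referral data collection follows randomisation. The GP criterion needs two weeks of those data from the control period. So no GP can have met it at randomisation, and the statement that all criteria are addressed by then cannot be true for GPs. This needs no assumption.

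**2. Window by sequence.** Inputs: 18 practices (Sample Size Calculation), 3 switching per month (Figure 1 text), collection from 1 September 2023, first starts in October 2023 and last completion at the end of February 2025 (Results). This gives 18 / 3 = 6 sequences. Twelve months ending in February 2025 puts the last start in March 2024. Starts are taken as the first of each month, and the window is the start date minus 1 September 2023.

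| Sequence | Start | Control days | 14 days as share | Latest day to begin and still qualify |
|---|---|---|---|---|
| 1 | Oct 2023 | 30 | 47% | 16 |
| 2 | Nov 2023 | 61 | 23% | 47 |
| 3 | Dec 2023 | 91 | 15% | 77 |
| 4 | Jan 2024 | 122 | 11% | 108 |
| 5 | Feb 2024 | 153 | 9% | 139 |
| 6 | Mar 2024 | 182 | 8% | 168 |

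The opportunity to qualify therefore depends on the randomised sequence.

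**3. The plan's own figure.** As a check on this layout, I used the stepped wedge generalised least squares variance with 18 monthly periods, the embedding and post-intervention months dropped, 60 consultations per practice-month, ICC 0.06, 10% against 6.3%, and categorical time. Power is 91.2% and the detectable difference at 90% power is 3.62 points, against the stated 90% and 3.7. The figure is reproduced, and the sample size is not in question.

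**4. Illustrative bias.** The documents give no number of late joiners, so the following are assumptions: 4 GPs per practice with 15 consultations a month each (4 x 15 = 60); 1 or 2 of the 4 join late in sequences 2-6, giving half a control month plus 11 intervention months; late joiners refer 3 points less often. The total variance is 0.10 x 0.90 = 0.09, of which 6% is practice variance and a share g is GP variance. The expected bias is the treatment element of

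(sum of D'V⁻¹D)⁻¹ (sum of D'V⁻¹d),

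summed over practices. D holds treatment and time, V is the covariance of the GP-month means, and d is -0.03 in late joiners' rows and 0 elsewhere. Each range below runs over linear and monthly time; the 1-3% row also runs over g.

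| GP share of variance g | 1 of 4 late (points) | 2 of 4 late (points) |
|---|---|---|
| 1-3% | -0.06 to -0.18 | -0.10 to -0.32 |
| 0.2% | -0.32 to -0.38 | -0.55 to -0.69 |
| 0 | -0.44 to -0.53 | -0.77 to -0.96 |

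Against 3.7 points, -0.06 is 2%, -0.18 is 5% and -0.32 is 9%. The last row contradicts its own premise: a 3-point gap between one GP in four and the rest implies a GP variance of 0.03² x 0.25 x 0.75 = 0.00017, and 0.00017 / 0.09 is about 0.2%. The bias is linear in d, so if late joiners refer 3 points more often, every sign reverses.

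**The case against.** The strongest reply is that the randomisation section is mainly about practices: its subject is general practices being recruited, enrolled and signed up, and at that level the protection is sound. That stands. Table 2 puts GP consent before allocation, and the Results section has GP recruitment starting in March 2023, well before collection began. The two-week rule in the recruitment section is a restriction. It can be read as a condition on GPs who have already consented, and it ensures that participating GPs supply some control data. The planned model also has a GP random effect and adjusts for GP-level factors, both of which limit any bias.

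A reader might therefore infer too much in saying that GPs do join with knowledge of the start date, or that the protection against recruitment bias fails altogether. The documents do not support either. Late entry is only one reading of the recruitment rule, and Table 2 points the other way. Nor do they establish that GPs who miss the two weeks are excluded from the analysis; that is not stated.

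The reply does not remove the timing conflict. Even if Table 2 is binding, the two-week criterion is decided after randomisation with the start date known, so GPs could still be selected out. The article's remark that knowing the allocation will not change standard practice concerns how GPs behave, not which GPs enter.

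**Conclusion.** The point stands at GP level. The statement that all inclusion criteria are addressed before randomisation conflicts with the GP criterion and the start of data collection, and the qualifying window runs from about 1 to about 6 months by sequence. Table 2, the recruitment rule and the analysis population need to be reconciled on when GP entry closes and who is analysed.

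No material threat to the primary result is shown. The number of late or excluded GPs is not given, so size and direction are unknown. The share of late joiners, their 3-point difference and the GP variance used above are all assumptions. With GP variance at 1-3% of the total, the illustrated bias is at most about a tenth of the target effect. Someone might take the values near half a point or a full point as the expected bias, but those need a GP variance at or near zero. This is a correction worth making because it is cheap and removes a selection step taken with the allocation known.

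**What to change.** 1. Define the primary analysis population as GPs who consented before the randomisation date, as Table 2 implies, whether or not they reached two weeks of control data. Analyse them by their practice's randomised step.
2. Put any GPs who consented later in a sensitivity analysis, and report by sequence how many joined late and how many missed the two weeks.
3. In Randomization and Blinding, limit the recruitment-bias statement to practices. Align the wording of Textbox 1, the recruitment section and Table 2 with it.

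The cost is mainly wording. If there are late joiners, some intervention-period consultations leave the primary analysis. GP consent dates must be taken from the signed consent forms; the article does not say that dates are recorded, so this needs confirming. A GP with no control data cannot be classified for the planned interaction with baseline referring level, which affects that analysis only.

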**Exclusion criteria**
Families:Children or young people who present to the general practice without a parent/guardian.Insufficient English.

### Recruitment

#### General Practices and GPs

An expression of interest will be distributed to practice managers, GPs, and practice nurses through the primary health networks (PHNs) [24], Central and Eastern Sydney, South Western Sydney, South Eastern NSW, and directly to other general practices in rural, regional, and remote areas in NSW. Interested general practices will be required to sign a memorandum of understanding with the research team adhering to the requirements of their participation, and sign a license agreement to install the clinical data extraction software tool GRHANITE [25]. GRHANITE is discussed in the Data Management Plan section. Each GP will be required to sign a participant information consent form (Section S1 in Multimedia Appendix 1) to participate in the trial. Any GP wanting to participate during the intervention phase must provide at least 2 weeks of control referral data. Each participating practice will receive a one-off AU $1000 (approximately US $655) payment to support the implementation of the trial into their practice. An ethics-approved poster will be available for practices to promote the GP-pediatrician coconsultation service and inform patients about the study.

#### Families/Caregivers

Caregivers of patients younger than 18 years who present to a participating general practice are invited to complete an anonymous, web-based survey about their perceptions and experience of the care received during a recent GP consultation (Section S4 in Multimedia Appendix 2). These surveys will be sent by each practice via a broadcast SMS text message on behalf of the research team to families/caregivers of patients younger than 18 years who have received care at the general practice, regardless of GP seen, in the 3 months preintervention (baseline) and in the 3 months before the SUSTAIN model of care (intervention) ends. In the final survey, caregivers will be invited to voluntarily participate in a qualitative interview via telephone/web-based video led by the implementation evaluation team for the trial.

### Randomization and Blinding

Participating practices will be randomized for intervention using a predetermined web-based randomization sequence generated by an independent trial statistician. Participating general practices will be randomly ordered in terms of when they switch from standard GP care to the SUSTAIN model of care by the independent statistician. To avoid recruitment bias in clusters, randomization will occur once all general practices have been recruited and enrolled; that is, after all inclusion and exclusion criteria are addressed, and all general practices sign the relevant trial agreements. Following randomization, practices will be unblinded to their allocation status/model of care start date. It is necessary for each general practice to know their randomization position to prepare for intervention, so allocation is not concealed. It is not anticipated that GPs knowing their randomization status will impact/change their standard practice due to their demanding workload. The research team is also unblinded to each practice’s allocation status to allow them to effectively engage with each practice to prepare their implementation schedule.

### Intervention

SUSTAIN is a 12-month-long virtual model of care offered to all consenting GPs in participating general practices. It consists of four components: (1) virtual GP-led, shared GP-pediatrician consulting sessions with patients younger than 18 years, (2) virtual pediatrician-led case discussion sessions, (3) phone/email pediatrician support, and (4) complimentary access to the internationally renowned SCHP learning platform (Figure 2).

**Figure 2. F2:**
[figure not shown]
SUSTAIN intervention (model of care components). GP: general practitioner.

During their 12-month intervention period, GPs may engage with any component of the model of care based on their needs, capacity, and learning style. The SUSTAN model of care will be delivered by a 1.0 FTE pediatrician (can be a shared position). The pediatricians will be employed through the SCHN.

### Data Management Plan

All participants (GPs and caregivers) will be assigned a unique numerical identifier (an ID code) generated in REDCap (Research Electronic Data Capture; Vanderbilt University) for use throughout the trial. A single electronic, password-protected database in REDCap will record all general practices, GP details, and survey data. Any data recorded will be stored on the secure University of New South Wales (UNSW) network drive on a password-protected computer and will be made available for importing into the project secure research environment. The project database will only be accessible by the designated research team members (investigators, statistician, and project managers) and hosted on the UNSW secure server, which meets security and ethical confidentiality requirements.

GRHANITE, developed and managed by the Health and Biomedical Informatics Center at the University of Melbourne (UoM), specifically designed for research purposes [25,26], extracts and curates the delivery of deidentified and encrypted primary care data to secure research data storage facilities. Person identifiers are removed from the data, in keeping with data custodian permission, and subject to ethics committee approval and legal agreement. Data extracted by GRHANITE will be stored in a Research Databank on the UoM Research Cloud, physically located within the UoM Secure Data Center. GRHANITE data will be made available to the research team from this databank via a UoM secure virtual research environment that gives researchers access to the data in a controlled manner. Upon completion of GRHANITE data extraction, only deidentified data will be transferred to the project analysis team, with a project ID unique to each patient. GRHANITE is only compatible with BP and medical director (MD) electronic medical records (EMRs), used by ≈90% of Australian general practices [27].

Patient confidentiality will be strictly held in trust by the participating investigators, research staff, and the sponsoring institution and their agents. No information concerning the trial or the data will be released to any unauthorized third party without the participant’s consent and written approval of the sponsoring institution.

All interview data will be transcribed and deidentified for analysis and will be stored in a restricted-access folder on UNSW network drives on a password-protected computer. Any personal information or quotes attributed to individual participants in published form will be anonymized.

